### Study procedures

Twelve visits are scheduled for this trial and a summary of study procedures for each visit is presented in Table 3. The expected duration of study participation is about 4–5 months. All patients must agree to use two reliable, effective contraceptive methods simultaneously for at least 7 days prior to the first dose of the study drug and for 6 weeks following the last dose of the study drug, unless absolute sexual abstinence is the chosen method of contraception. This is because mycophenolate mofetil is known to cause a high frequency of miscarriage (~ 50%) and severe birth defect in the unborn baby [26, 27].

**Table 3 Tab3:** Scheduled visits and assessments

Procedures	Study Visits											
	SV	C_1_w_0_	C_1_w_1_	C_1_w_2_	C_1_w_4_	C_2_w_2_	C_2_w_4_	C_3_w_2_	C_3_w_4_	C_4_w_2_	C_4_w_4_	FV
Informed consent obtained	×											
Inclusion/exclusion criteria assessments	×											
History taking	×											
Physical examination	×	×	×	×	×	×	×	×	×	×	×	×
ECOG status	×											
Electrocardiogram	×											
Lab test for complete blood count	×			×	×	×	×	×	×	×	×	×
Lab test for fasting blood glucose	×											
Other lab tests^(a)^	×			×	×		×		×		×	×
Circulating tumor cells		×^(b)^	×^(b)^	×		×		×		×		
Biobank collection	×				×		×		×		×	×
Urine analysis^(c)^	×			×	×		×		×		×	×
Stool examination	×											×
Pharmacokinetic study^(d), (e)^		×	×									
Pain score & Quality of life		×			×		×		×		×	×
Review of concomitant medications	×	×	×	×	×	×	×	×	×	×	×	×
Monitoring for adverse events			×	×	×	×	×	×	×	×	×	×
Tumor assessment^(f)^	×						×				×	

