SV = screening visit; C_x_w_y_ = cycle x week y; FV = final visit. ^(a)^ Lab tests include Na, K, Cl, HCO3, Ca, Mg, P, albumin, AST, ALT, ALP, total bilirubin, direct bilirubin, BUN, Cr, PT, PTT, INR, and LDH; ^(b)^ Blood obtained from the pharmacokinetic study will be used for measurement of circulating tumor cells on C_1_W_0_ and C_1_W_1_ so that no additional blood samples will be collected; ^(c)^ Urine analysis includes a urine pregnancy test for a female patient of childbearing age; ^(d)^ Blood samplings (at 0, 0.5, 1, 1.5, 2, 3, 4, 6, 8, 10, and 12 h); ^(e)^ Additional samplings for drug monitoring may be required when drug dosage is modified (after ≥7 days of drug administration with an adjusted dose level); ^(f)^ Tumor assessment by a computerized tomography (CT) scan (of the chest ± other organs, if required) or magnetic resonance imaging (MRI), done at baseline, 8 ± 1 weeks and 16 ± 1 weeks after initiation of study drug administration; in case of objective tumor response (complete response or partial response), confirmatory imaging studies will be performed at least 4 weeks after initial documentation of response

There are three drug regimens to be used for prophylaxis of possible infection during study participation: (1) ivermectin (12 mg/day) for 2 days before Cycle 1, Week 0 [28], (2) trimethoprim-sulfamethoxazole (160/800 mg/day) once daily from Cycle 1, Week 1, until discontinuation of mycophenolate mofetil [29], and (3) acyclovir (400 mg/day) twice daily from Cycle 1, Week 1, until discontinuation of mycophenolate mofetil [30]. No evidence of PK drug-drug interactions between any of these regimens and mycophenolate mofetil is reported [31].

Should mycophenolate mofetil prove beneficial to some patients (i.e., evidence of stable disease or partial response) at the end of the treatment period (on Week 16), the study treatment will be given to those patients in the extension period until one of the withdrawal criteria is met. Additional visits will be scheduled during the extension period (Table 4).

**Table 4 Tab4:** Additional visits and assessments in the extension period

Procedures	Study Visits								
	C_5_w_2_	C_5_w_4_	C_6_w_2_	C_6_w_4_	C_7_w_2_	C_7_w_4_	C_x_w_2_	C_x_w_4_	FV
Physical examination	×	×	×	×	×	×	×	×	×
Lab test for complete blood count	×	×	×	×	×	×	×	×	×
Other lab tests^(a)^		×		×		×		×	×
Circulating tumor cells	×		×		×		×		
Biobank collection		×		×		×		×	×
Urine analysis^(b)^		×		×		×		×	×
PK study^(c)^									

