Pain score & Quality of life		×		×		×		×	×
Review of concomitant medications	×	×	×	×	×	×	×	×	×
Monitoring for AEs	×	×	×	×	×	×	×	×	×
Tumor assessment^(d)^						×			

C_x_w_y_ = cycle x week y; FV = final visit. ^(a)^ Lab tests include Na, K, Cl, HCO3, Ca, Mg, P, albumin, AST, ALT, ALP, total bilirubin, direct bilirubin, BUN, Cr, PT, PTT, INR, and LDH; ^(b)^ Urine analysis includes a urine pregnancy test for a female patient of childbearing age; ^(c)^ Additional samplings for drug monitoring (at 0, 0.5, 1, 1.5, 2, 3, 4, 6, 8, 10, and 12 h) may be required when drug dosage is modified (after ≥7 days of drug administration with an adjusted dose level); ^(d)^ Tumor assessment by a CT scan (of the chest ± other organs, if required) or MRI, done at 12-week interval (±1 week); in case of objective tumor response (complete response or partial response), confirmatory imaging studies will be performed at least 4 weeks after initial documentation of response

The final visit will be scheduled in 4 weeks (±1 week) after the treatment with mycophenolate mofetil has stopped. After completion of the study, follow-up survival information will be collected by either clinical visit or telephone contact every 12 weeks (±1 week) until death.

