### Statistical analysis plan

All patients who receive at least one dose of mycophenolate mofetil will be included in an intention-to-treat analysis. Patients’ baseline demographics will be summarized using descriptive statistics. Study drug administration will be described in terms of the total number of cycles (or days) administered, the median (range) of cycles (or days) administered, dose intensity, and reasons for deviations from planned therapy. Adverse events will be collected after the patient has taken the first dose of mycophenolate mofetil.

The PFS at 16 weeks or DCR (the primary endpoint) will be measured as a binary variable: DCS or DCF. The PFS and OS will be summarized using the Kaplan-Meier method and displayed graphically as appropriate. For patients lost to follow-up, they will be censored at the date of the last follow-up visit. Median PFS and OS (and their corresponding 95% confidence intervals) will also be provided.

All statistical analysis will be executed using IBM SPSS Statistics for Windows, version 22.0, with a *p* value of less than 0.05 considered to indicate statistical significance. It is possible that the decision rule of this single-arm, two-stage phase II clinical trial may need to be adapted from the original plan [33]. If the attained sample size at the end of this study is different from the one that is initially planned due to any reason, a statistical testing will be conducted by calculating the *p* value with the sample size at the stopping stage conditioned on the observed value [34, 35]. The Jennison-Turnbull confidence interval may be used by treating the observed sample size at the stopping stage like the planned sample size [36].

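### Patients lost to follow-up are censored for PFS at the last visit, not the last tumour assessment, so the secondary Kaplan-Meier PFS curve can be biased upward

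*Protocol article*

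**What the plan says.** In the Statistical analysis plan section of the protocol article, three sentences follow one another. The first names both endpoints: "The PFS and OS will be summarized using the Kaplan-Meier method and displayed graphically as appropriate". The second gives the only censoring rule: "For patients lost to follow-up, they will be censored at the date of the last follow-up visit". The third promises the summaries: "Median PFS and OS (and their corresponding 95% confidence intervals) will also be provided". No separate date is given for PFS.

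The calendar is in Study procedures:

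- **Scans.** In the main period they are "done at baseline, 8 ± 1 weeks and 16 ± 1 weeks after initiation of study drug administration" (Table 3, footnote f). In the extension they are 12 weeks apart (Table 4, footnote d).
- **Visits.** "Twelve visits are scheduled for this trial". By Table 3 they fall at weeks 0, 1, 2 and 4 and then every two weeks to week 16. Table 4 continues every two weeks.
- **Final visit.** It comes four weeks after the drug stops. Neither table marks a tumour assessment there.
- **Afterwards.** "follow-up survival information will be collected by either clinical visit or telephone contact every 12 weeks", until death, with no imaging stated.

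PFS as a time variable is a secondary endpoint (Study endpoints). The primary endpoint, PFS at 16 weeks, is analysed as a binary success or failure.

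**The concern.** A censoring date tells Kaplan-Meier that the patient was known to be event-free up to that day. For OS, a visit establishes this. For PFS determined by imaging, a visit without a scan does not. Under the stated rule, a lost patient stays in the PFS risk set, counted as progression-free, between the last scan and the last visit. The added time can only raise the estimated curve relative to censoring at the last assessment.

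Such patients are foreseeable. The Withdrawal criteria include toxicity, noncompliance, intercurrent illness and deterioration in health, and any of these can end treatment before the next scan. With 27 patients, a few censoring dates can move the curve. What is at stake is how a secondary result is read, not the go/no-go decision.

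**Working it through.** **Inputs.** The visit and scan calendar is as above. The 16-week success proportions are 0.12 (p0) and 0.32 (p1), from Sample size determination. The article states no median PFS to reproduce. Its design does reproduce: 19 then 27 patients, continuing with at least 3 successes and succeeding with at least 6, gives exact α = 0.0936 and power = 0.9000. The loss rate is not given, so 10%, 20% and 30% are assumed.

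**Step 1: gap between last scan and last visit (nominal weeks, ignoring the ±1-week windows).**

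- Main period, on treatment: visit at week 14, scan at week 8; 14 − 8 = 6 weeks.
- Extension, on treatment: visit at week 26, scan at week 16; 26 − 16 = 10 weeks.
- Drug stopped at week 14, final visit at week 18, scan at week 8: 18 − 8 = 10 weeks.
- Drug stopped at week 26, final visit at week 30, scan at week 16: 30 − 16 = 14 weeks.
- Longer still if survival contacts count as follow-up visits.

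**Step 2: does the median have to move?** Suppose events occur only at the week-8 and week-16 scans, and a share u is never scanned but stays at risk. Then S(t) = u + (1 − u)·S₀(t). With exponential PFS, S₀(8) = √S₀(16).

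- S₀(16) = 0.12: S₀(8) = 0.346. For u = 5%, 10%, 15%, S(8) = 0.38, 0.41, 0.44. All are below 0.5, so the median stays at week 8.
- S₀(16) = 0.32: S₀(8) = 0.566. At u = 15%, S(8) = 0.63 and S(16) = 0.42, so the median stays at week 16.

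The curve rises but the median does not.

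**Step 3: simulation, ordinary loss between scheduled visits.** Exponential PFS on the protocol calendar; loss either unrelated to progression or caused by unseen progression; 0%, 30% or 60% of events dated between scans. In trials of 27, the visit rule minus the last-assessment rule shifted the median by 0 to +0.66 weeks on average. The median rose in 0–35% of trials and fell in none. The shift was exactly 0 when all events were dated at scans. Large-sample week-16 PFS, p = 0.32, 30% loss:

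| Loss | Events between scans | Visit rule | Last assessment | Full follow-up |
|---|---|---|---|---|
| Unrelated | 0% | 0.316 | 0.316 | 0.319 |
| Unrelated | 60% | 0.312 | 0.299 | 0.316 |
| Linked to progression | 0% | 0.425 | 0.425 | 0.322 |
| Linked to progression | 30% | 0.397 | 0.390 | 0.321 |

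**Step 4: simulation, followed without imaging and then lost.** A share f is assigned to stop the drug without progression at a uniform time in weeks 0–16. These patients have no further scans, attend the final visit, may have survival contacts every 12 weeks, and are then lost (mean 12 weeks after the final visit, assumed). Events are dated at scans. The median shift is for the rule that counts survival contacts, in trials of 27 where both medians were reached.

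| p | f | Week-16 PFS, contacts count | Final visit only | Last assessment | Mean median shift (weeks) | Trials with a rise |
|---|---|---|---|---|---|---|
| 0.12 | 10% | 0.147 | 0.130 | 0.119 | 0.21 | 2.6% |
| 0.12 | 20% | 0.181 | 0.147 | 0.120 | 0.55 | 6.8% |
| 0.12 | 30% | 0.218 | 0.163 | 0.119 | 1.06 | 13.1% |
| 0.32 | 10% | 0.345 | 0.333 | 0.320 | 0.86 | 9.5% |
| 0.32 | 20% | 0.377 | 0.351 | 0.322 | 1.73 | 18.1% |
| 0.32 | 30% | 0.406 | 0.366 | 0.322 | 2.69 | 26.4% |

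The median fell in no trial. Here last-assessment censoring recovers the true 0.12 and 0.32.

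**The case against.** The strongest case against has five parts.

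1. **Scope.** The rule covers only patients lost to follow-up. It does not govern those who stop the drug and remain in contact. This stands.
2. **Size.** A reader might infer that median PFS is necessarily overstated, or apply the Step 2 formula to week 16 and read 16–25% in place of 12% (u = 5–15%) as the effect of this rule. The documents support neither. The formula counts every unscanned patient still in contact, lost or not, and the median does not move in that model. A reader might also put the on-treatment gaps at 8 and 12 weeks, but that requires attending a scan visit without being scanned.
3. **The alternative is not always better.** When loss is unrelated to progression and many events are dated between scans, the visit rule is closer to full follow-up (0.312 against 0.316) and last-assessment censoring sits low (0.299). When loss is caused by unseen progression, both rules are too high and changing the date removes little (0.397 to 0.390, against 0.321). This also stands, and it confines the clear benefit to patients followed without imaging.
4. **Favourable reading.** The Interventions section uses the term follow-up visit for clinic visits where tablets are returned, so telephone contacts may not count. Even then, the scan-free final visit leaves about 10 unassessed weeks after a stop at week 14, and the final-visit-only column still exceeds the truth.
5. **Condensed article.** Censoring detail often sits in an analysis plan that is not shown. Here, though, the article does not omit the rule: it states one, in a sentence that serves PFS and OS together.

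**Conclusion.** The point holds in a limited form. For patients lost to follow-up, the stated date can credit unassessed time as progression-free: about 6 weeks (main period) or 10 weeks (extension) on treatment, and about 4 more when the final visit is the last one. The Kaplan-Meier PFS curve can therefore be biased upward. The visit rule is itself the main cause when patients are followed without scans; when loss is linked to unseen progression it adds only modestly to a bias that is present anyway.

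The mean median shift against last-assessment censoring is 0 to about 0.7 weeks for ordinary loss and about 0.2 to 2.7 weeks when patients are followed unscanned. These figures rest on assumed loss of 10–30%, exponential PFS and assumed contact patterns; the article gives no loss rate.

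A reader might infer that the trial's decision is at risk. It is not: the primary endpoint is binary, and the Simon rule and sample size do not use this curve. The 1.8-month median time to progression in Sample size justification is background for p1, and no comparison of median PFS with it is planned.

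**What to change.** Replace the shared sentence with one rule per endpoint:

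- **PFS:** patients without documented progression or death are censored at the last evaluable tumour assessment showing no progression, or at the first-dose date if there is none after baseline. Survival contacts do not extend PFS.
- **OS:** patients not known to have died are censored at the date last known alive.

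The visit-based PFS rule may remain as a sensitivity analysis. It is worth keeping, because the two rules err in different directions in some settings. Reporting the number of lost patients and each gap between last scan and last visit would show how much the choice matters, and would flag possible progression-linked loss, which neither date repairs.

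The cost is a sentence or two of text and no extra patients, visits or scans. The PFS estimate may be slightly less favourable, and the late part of the curve slightly less precise.

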### Sample size determination

The sample size was calculated according to the Simon’s minimax two-stage design, with PFS at 16 weeks as the primary endpoint. PFS is dichotomized according to whether PFS is ≤16 weeks (defined as disease control failure (DCF)) or > 16 weeks (defined as disease control success (DCS)). Therefore, treatment with mycophenolate mofetil will be considered successful if the 16-week radiological evaluation indicates stable disease, partial response, or complete response, as defined by the RECIST criteria version 1.1. Patients alive after 16 weeks without signs of progression will be regarded as DCS.

The sample size was calculated under a hypothesis of interest in which DCS at 16 weeks is ≥32% (*p*_1_ = 0.32, the minimal proportion of successes that makes the experimental treatment worth further studies) and a null hypothesis in which mycophenolate mofetil reaches a DCS at 16 weeks < 12% (*p*_0_ = 0.12, the proportion of successes that implies no clinically worthwhile activity of the experimental treatment). Setting *α* = 0.10 (where *α* represents the probability of failing to reject a treatment with response probability ≤*p*_0_) and *β* = 0.10 (where *β* represents the probability of rejecting a treatment with response rate ≥ *p*_1_), this condition requires 19 patients to be enrolled in Stage 1. Recruitment will continue to reach a total of 27 patients if the number of DCS among the first 19 patients is at least 3; otherwise, the trial will be stopped for inefficacy after analysis of 19 patients. As per the study protocol, mycophenolate mofetil will be deemed promising and worth further studies if at least 6 DCS is observed at the end of the study.

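### The general p<0.05 threshold does not exempt the primary endpoint, although the design uses alpha 0.10; if the attained sample size is off plan, the two levels can give opposite conclusions

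*Protocol article*

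**What the plan says.** Under Sample size determination the article states: "The sample size was calculated according to the Simon’s minimax two-stage design, with PFS at 16 weeks as the primary endpoint". The null DCS rate is 12% and the rate of interest is 32%. The error rates follow: "Setting *α* = 0.10", with beta also 0.10. Stage 1 has 19 patients and the trial continues if at least 3 are DCS. The final rule is a count: "mycophenolate mofetil will be deemed promising and worth further studies if at least 6 DCS is observed at the end of the study".

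Under Statistical analysis plan, one sentence covers all analyses and sets a p "value of less than 0.05 considered to indicate statistical significance". It names no exception and does not say whether p is one- or two-sided. The same paragraph allows the decision rule to be adapted. If the attained sample size differs from plan for any reason, "a statistical testing will be conducted by calculating the" p value at the stopping stage, and a Jennison-Turnbull interval may be used. No significance level is given for that test and no confidence level for that interval.

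**The concern.** The article fixes two error levels, and the primary endpoint falls under both. The go/no-go rule was built at 0.10. The only threshold stated for reading a p value is 0.05, and it stands in the same paragraph as the off-plan test. When the sample size departs from plan, the trial's main conclusion can therefore depend on which level the analyst applies, and that choice could be made after the count is known.

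The article itself makes a departure plausible:

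- Withdrawal criteria replaces some patients who leave in the first four weeks, while the analysis keeps everyone who took one dose. The analysed number can therefore exceed 27.
- Sample size justification says accrual may be slow, so fewer than 27 is also possible.

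What is at stake is the 90% power on which 19 and 27 were chosen, and a single pre-specified standard for calling the drug promising.

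**Working it through.** **Inputs** (Sample size determination): p0 = 0.12, p1 = 0.32, n1 = 19, continue if X1 ≥ 3, N = 27, success if X ≥ 6. The level is treated as one-sided, as a Simon design is by construction; the article does not say so in words.

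**Formula.** The probability of passing Stage 1 and ending with at least k DCS among N patients is

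R(N, k, p) = Σ (x from 3 to 19) P[Bin(19, p) = x] · P[Bin(N − 19, p) ≥ k − x].

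At p = 0.12 this is the two-stage exact p value for k DCS. At p = 0.32 it is the power of a cut-off at k.

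**Step 1: reproduce the plan's design.** For N = 27, k = 6, p = 0.12:

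- x = 3: 0.21657 × 0.06079 = 0.01316
- x = 4: 0.11813 × 0.24804 = 0.02930
- x = 5: 0.04832 × 0.64037 = 0.03095
- x ≥ 6: 0.02022 × 1 = 0.02022
- Sum: 0.0936

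At p = 0.32 the same sum is 0.9000. A full minimax search at alpha 0.10 and beta 0.10 returns the stated design: 19, continue at ≥3, 27, success at ≥6. The sample size calculation is correct.

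**Step 2: the boundary at N = 27.** For k = 7, R = 0.0360 at 12% and 0.8077 at 32%. So p is 0.0936 for 6 DCS and 0.0360 for 7 DCS, and only exactly 6 DCS lies between the two levels. Its probability is 0.0936 − 0.0360 = 0.058 at 12% and 0.9000 − 0.8077 = 0.092 at 32%. Single-stage calculations for 6/27 also exceed 0.05: 0.097 exact one-sided, 0.128 exact two-sided, 0.051 one-sided normal approximation without continuity correction.

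**Step 3: sample sizes where the p value is the scheduled test.** Stage 1 is held at 19 patients with continuation at ≥3.

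| N | p, 5 DCS | p, 6 DCS | p, 7 DCS | p, 8 DCS | Cut-off at 0.10 | Cut-off at 0.05 |
|---|---|---|---|---|---|---|
| 23 | 0.132 | 0.0496 | 0.015 | 0.004 | 6 | 6 |
| 24 | 0.149 | 0.059 | 0.019 | 0.005 | 6 | 7 |
| 25 | 0.166 | 0.070 | 0.024 | 0.007 | 6 | 7 |
| 26 | 0.182 | 0.082 | 0.030 | 0.009 | 6 | 7 |
| 28 | 0.213 | 0.106 | 0.043 | 0.015 | 7 | 7 |
| 29 | 0.228 | 0.119 | 0.0505 | 0.018 | 7 | 8 |

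The levels disagree at 24, 25, 26 and 29 and agree at 23 and 28.

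**Step 4: effect on power.** At N = 26 and p = 0.32, R(26, 6) = 0.881 and R(26, 7) = 0.773. Applying 0.05 instead of 0.10 costs 0.881 − 0.773 = 0.11.

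**Step 5: the interval.** Solving R(27, 6, p) = level for p gives the lower limit for 6/27 under the two-stage ordering: 0.122 at one-sided 0.10, 0.102 at 0.05 and 0.087 at 0.025. Only the first excludes 12%, so the unstated confidence level matters if the interval informs the decision.

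**The case against.** The strongest reply is that the planned trial has one decision rule and no contradiction. Sample size determination fixes the count at 6, and the analysis section schedules no primary p value at 27 patients. On this reading the 0.05 sentence is routine software wording. That largely stands. A reader might infer that 6/27 is formally both promising and not significant, or that the plan really needs 7/27 with power 0.81. The documents do not support this, because the specific count rule governs at 27. What remains there is narrower: a p value reported for exactly 6 DCS would carry the wrong label.

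A reader might also infer that any one-patient departure moves the bar. It does not: at 28 patients the cut-off is 7 at both levels. The conflict depends on the attained number.

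Nor is it a separate defect that a conventional 95% exact interval for 6/27 (8.6% to 42.3%) includes 12%. That is expected at the boundary of a one-sided 0.10 design, and the only 95% intervals the article plans are for median PFS and OS.

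Finally, the methods cited for the off-plan test, or a fuller analysis plan, might carry over the design alpha. Neither is at hand. This does not remove the point, because the article itself states a threshold, applies it to all analyses and exempts nothing.

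**Conclusion.** The inconsistency is real and bears on the primary conclusion, within limits. The design level is 0.10 and the only level stated for p values is 0.05. The sample size, Stage 1 rule and final count are correct.

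- At 27 patients the effect is confined to how exactly 6 DCS is described, an outcome with probability 9.2% at a 32% DCS rate and 5.8% at 12%.
- Off plan, where the p value is the test, the conclusion reverses for 6 DCS at 24 to 26 patients and for 7 DCS at 29. At 26 patients the loss of power is about 11 percentage points.

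These figures assume a one-sided two-stage exact p value with Stage 1 run as planned. A departure within Stage 1 would change them, but would not settle which level applies.

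**What to change.** Amend the Statistical analysis plan section to state that:

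1. the primary endpoint is judged one-sided at the design alpha of 0.10, by the count rule at 27 patients and by the two-stage exact p value if the attained number differs;
2. any Jennison-Turnbull interval used for that decision has the matching level (a one-sided 90% lower bound, equivalent to the lower limit of a two-sided 80% interval);
3. p<0.05 applies only to secondary or exploratory analyses.

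The cost is a few sentences, submitted to the ethics committees as a protocol modification and settled before the primary data are analysed. The sample size, Stage 1 rule and the rule of at least 6 of 27 stay unchanged. If the sponsor does intend 0.05 for the primary endpoint, wording alone is not enough: the cut-off at 27 becomes 7 with power 0.81, and a minimax search for 90% power gives 35 patients (19 in Stage 1, continue at ≥3, success at ≥8; alpha 0.049, power 0.902).
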